#### Strategies to improve adherence to interventions {11c}

One week after the agreed appointment, the study nurse calls the intervention patients to ask whether they have kept their appointment with the nephrologist and, if not, whether the nurse should arrange a new appointment.

#### Relevant concomitant care permitted or prohibited during the trial {11d}

Any concomitant treatments and measures are permitted during the trial.

#### Provisions for post-trial care {30}

No provisions are made for ancillary care, post-trial care or compensation. Patients in the control group are treated as in routine care and it can be expected that the intervention, consisting of an appointment with a nephrologist, will not be detrimental to the patient.

### Outcomes {12}

#### Primary endpoint

Difference in mean change in eGFR in ml/min/1.73 m^2^ (after chronic kidney disease epidemiology collaboration [CKD-EPI]) between the intervention and control group from baseline to 12 months after hospital discharge

The eGFR was chosen as the primary parameter because it is considered a good indicator for the assessment of kidney patients and has also been used in numerous nephrology studies over time [18].

#### Secondary endpoints

Differences between intervention and control group, 12 months after hospital discharge:Difference in proportion (%) of patients with controlled blood pressure (≤ 140/90 mmHG)For diabetics: difference in proportion (%) with guideline-compliant HbA1c (6.5 to ≤ 7.5%)Difference in proportion (%) of patients with non-guideline-compliant care about the prescription of selected medication groups (including statins, RAS blockers, ARBs and ACEIs; based on pre-specified ATC codes classified as non-guideline-compliant) according to the assessment of medication plans by consultant nephrologistsDifference in the proportion (%) of patients with non-guideline-compliant medication (resulting from the aforementioned assessment of medication plans by several consultant nephrologists)Difference in the mortality rate (%)

#### Health economics

Intervention costs and costs of medical service utilisation in relation to the primary and secondary endpoints based on cost-effectiveness analyses

#### Process quality, acceptance and feasibility

Comparison between intervention and control group:Difference in proportion (%) with a nephrology specialist consultation at 3 months from dischargeIntervention patients:Perceived quality of care (Patient Reported Outcome [PRO], 3 + 12 months), after 3 months incl. factors from the patient’s perspective that led to non-utilisation of nephrology carePerception of illness (PRO: Brief-Illness-Perception-Questionnaire [BIPQ], 3 + 12 months)Knowledge about kidney disease (PRO: Perceived Kidney Knowledge Survey [PIKS], 3 + 12 months)Health-related quality of life (PRO: Short Form 12 [SF12], 3 + 12 months)Control patients:Perception of illness (PRO: BIPQ, 12 months)Knowledge about the kidney disease (PRO: PIKS, 12 months)Health-related quality of life (PRO: SF12, 12 months)GPs/specialists:Acceptance and feasibility of this new form of care (risk-based appointment scheduling): Semi-structured interviews with specialists (*N* = 4, 30 min) and GPs (*N* = 8, 20 min)

### Participant timeline {13}

#### Screening

For newly admitted patients, the information on the patient in the hospital information system (HIS) is checked for known concomitant renal disease (ICD10 codes: N04.9, N17.99, N18.1-0.9, N19, R31, R80) or newly detected impaired renal function (eGFR < 60 ml/min/1.73 m^2^). If chronic renal disease is indicated, the patient’s 5-year ESRD risk will be estimated using the KFRE formula.

#### Evaluation of eligibility

If a study patient meets all inclusion criteria and none of the exclusion criteria, this is indicated to the corresponding study nurse in the HIS. In the first step, the study nurse classifies this patient (Fig. 2), assessing whether the patient has chronic renal disease based on the available patient data and entries in the HIS. If chronic renal disease appears certain, the patient will be informed about the study and asked for consent.

**Fig. 2 Fig2:**
[figure not shown]
Patient enrolment and follow-up in the MinDial study. Generally, eligibility is assessed by the study nurses. In doubtful cases, the decision for or against inclusion is made by study physicians, as detailed in this section

#### Consultation (study physicians)

If the study nurse cannot determine a definite chronic renal disease or study eligibility appears questionable due to critical health conditions (infirm prognosis, the patient may not survive the study), the electronic medical record will be forwarded to a study physician for evaluation. Therefore, a special mask implemented for this study in HIS is used, where the study nurses can tag a patient and additionally leave a note with the emerged question. The next time the patient is checked by the study doctor, he can immediately see the marked patients, process the requests and mark the patients back for the study nurses.

#### Recruitment (or exclusion from the study)

After a positive assessment of the patient by the study nurse or study physician, the informed consent form and an initial questionnaire are printed for the corresponding patient. After the study nurse has informed the patient about the study and the patient or the legal guardian has consented to the study participation, the patient is moved to the category ‘has consented’ in the HIS, and the informed consent form, as well as the initial questionnaire, is scanned and stored in the HIS.

The exclusion of patients from the study is documented with corresponding reasons.

**Patient characteristics (QN)**					
Weight	X				BL
Height	X				BL
Education level	X				BL
Living situation	X				BL
Smoking status	X				BL
General health condition	X				BL
Health literacy	X				BL
**Known diagnoses (HIS)**					
Chronic kidney disease	X				BL
Hypertension	X				BL
Diabetes	X				BL
Heart attack	X				BL
Charlson Index	X				BL
**Lab values (HIS)**					
Serum creatinine	X			X	PE
eGFR	X			X	PE
KFRE score	X				IC
HbA1c/glycosylated hemoglobin	X			X	BL | SE
Blood pressure (diast./syst.)	X			X	BL | SE
**Assessment of medication at discharge (HIS)**					
Guideline compliance	X				BL
Antihypertensives count	X				BL
ACEI/ARB/sartans	X				BL
SGLT2 inhibitors	X				BL
Statins	X				BL
Nephrotoxic medication	X				BL
**Assessment of medication at 12-month FU (GP/specialist)**					
Guideline compliance				X	SE
Antihypertensives count				X	SE
ACEI/ARB/sartans				X	SE
SGLT2-inhibitors				X	SE
Statins				X	SE
Nephrotoxic medication				X	SE
Vital status				X	SE
New onset diabetes mellitus				X	SE
**Medication costs (GP/specialist)**					
Name of drug/active ingredient/dosage/daily dose				X	HE
**Evaluation of intervention by patient (QN)**					
Appointment attended		X			Pr
Reasons for non-attendance		X			Pr
New appointment		X			Pr
Evaluation of appointment scheduling		X			Pr
Evaluation of consultation		X			Pr
Overall evaluation		X			Pr
**Evaluation of intervention by GP/specialist**					
GP (interview)				X	Pr
Nephr. specialist (interview)				X	Pr
**Utilization (QN)**				X	
Number of GP visits		X	X	X	HE
Number of specialist visits with date		X	X	X	HE
**PROs for process evaluation (QN)**					
Knowledge about kidney disease (PIKS)		X	X		Pr
Health-related quality of life (SF12)		X	X		Pr
Perception of illness (BIPQ)		X	X		Pr
**Costs of intervention (study nurse)**					
Working hours of study nurse	X	X			HE

*Abbreviations: ACEI* angiotensin-converting enzyme inhibitor, *ARB* angiotensin-receptor blockers, *BIPQ* Brief Illness Perception Questionnaire, *BL* baseline, *eGFR* estimated glomerular filtration rate, *FU* follow-up, *GP* general practitioner, *HE* health economics, *HIS* hospital information system, *IC* inclusion criterion, *KFRE* kidney failure risk equation, *Orga* organisation, *PE* primary endpoint, *PIKS* Perceived Kidney Knowledge Survey, *Pr* process evaluation, *PRO* patient-reported outcome, *QN* questionnaire, *SE* secondary endpoint, *SF12* Short Form 12, *SGLT2* sodium-glucose co-transporter 2

To document serum creatinine, KFRE score, blood pressure and HbA1c in the eCRF, all values are taken at a time interval around the date when the KFRE score is ≥ 15% (date of laboratory determination before 20 June 2023) or ≥ 9% (since 20 June 2023) for the first time in the current case.

#### Follow-up

##### Three-month follow-up after discharge (intervention patients)

Three months after discharge, intervention patients are contacted by mail and asked to fill out a questionnaire. Patients are asked whether they utilised the appointment by the nephrologist and if yes, how they assess the benefit of this referral. In addition, their quality of life (SF12), the knowledge about their kidney disease (PIKS), and how they perceive their disease (BIPQ) are asked via standardised questionnaires.

##### Twelve-month follow-up (all patients)

One year after discharge from the hospital, a follow-up is performed for each patient regarding renal function, HbA1c, blood pressure, medication, frequency of physician visits, quality of life, knowledge about the disease and illness perception. For this purpose, the GP and/or nephrologist are contacted by the study nurse by mail and/or phone to check the vital status of the patient and to request laboratory data concerning serum creatinine and Hba1c in diabetic patients, as well as the latest three blood pressure measurements, the number of patients visits during the last year, incident diabetes and the actual medication (via the standardised medication plan). The medication is assessed whether relevant medication classes are included (antihypertensives, statins, ACE inhibitors or RAAS blockers, and SGLT2).

The data collected at the 3-month and 12-month follow-ups are detailed in Table 1, together with the baseline data.

#### Questionnaires

In principle, the questionnaires are to be answered by the study participants themselves. If this is not possible for elderly or mentally incompetent patients, the legal guardian can answer the questionnaires for the patient. It is documented whether the answers were given exclusively by the caregiver/relatives or by the patients themselves.

### Sample size {14}

#### Original sample size calculation (before shifting from 4 to 8 clusters)

The sample size calculation was based on the primary endpoint. If after 12 months there is a mean difference in the decline of eGFR of 2 ± 4 ml/min/1.73 m^2^ (according to CKD-EPI; Cohen’s *d* = 0.5) between the control and intervention groups, in the cross-sectional complete cluster-randomised design chosen here (4 clusters, 4 steps, 5 measurement time points/periods), a difference can be detected in a linear mixed model with the Wald *z*-test for equality of means at the two-sided significance level *α* = 5% with a power of 80%, when 340 observations are available (PASS, version 15.0.3). Here, an intra-cluster correlation coefficient of 0.02 was assumed; this magnitude seems realistic, since the intervention is not directed at the treating physicians in the hospitals, but at the patients [19]. Furthermore, the assumed standard deviation of σ = 4 ml/min/1.73 m^2^ (assuming an eGFR variability [20] of 10% of the maximum eGFR of 40 ml/min/1.73 m^2^ expected in the patient population) seems realistic, and the mean difference of 2 ml/min/1.73 m^2^ seems achievable as well as clinically relevant [4]. Since we anticipate a drop-out of 20% at 12 months follow-up, *n* = 425 patients should be enrolled in the study, 85 in each of the 3-month periods until the next change of a cluster to the intervention phase.

#### Updated power calculation for the stepped-wedge design with 8 clusters

Before the start of the project, it was assumed that the shift from control to intervention conditions would have to take place simultaneously at all sites of a hospital (each with two sites) and that a design with four clusters would therefore have to be used. As it became clear that the eight sites were independent of each other in this respect, a design with one cluster per site was used instead, to improve the statistical power with the same use of resources.

An analysis of hospital data from 2020/21 after the project started had shown that recruitment numbers were expected to vary widely between sites in some cases. Assuming that 340 patients with complete follow-up would be recruited as planned, the following distribution among the 8 sites could be expected: 77, 63, 50, 37, 37, 34, 25 and 17 participants. By switching to a design with 8 clusters (one cluster per site) and under otherwise unchanged assumptions for the sample size calculation, a power of 87.5% was now expected before randomisation (R version 4.1.3, CRTpowerdist version 0.4.0 [21]). Since the actual power depends on the randomisation result, randomisation was performed under the constraint of largely balanced expected intervention and control group sizes. For this purpose, the set of possible randomisation outcomes was restricted to those where a maximum size difference between the intervention and control group of 20 subjects was expected. This corresponded to the exclusion of the less balanced half of all theoretically possible randomisations.

#### Second update of the power calculation (based on interim sample size)

In the fourth quarter of 2023, the statistical power was recalculated. In contrast to the previous calculations, actual recruitment figures were taken into account for each site and recruitment period (for periods 1–7; projections based on past recruitment numbers were used for periods 8–13). For an optimistic prediction of future recruitment numbers, the mean values of the three stronger recruitment periods were assumed. According to this prediction and factoring in a 20% drop-out rate, 286 patients with complete follow-up are expected to be available for the final analysis.

Considering the slow recruitment, it was decided to switch to one-sided testing to increase statistical power. In the original planning, impartial two-sided testing was planned, which would have allowed verification of both an advantage and a disadvantage of the intervention. On the one hand, it is much more relevant in the context of health care to prove an advantage of the intervention than a disadvantage. On the other hand, it is more likely to assume an advantage (of unknown magnitude) than patients getting worse in terms of their kidney function as a result of an appointment with a nephrologist.

With one-sided testing and otherwise unchanged assumptions (regarding effect size, intra-cluster correlation coefficient and significance level), this corresponds to a power of 72.1% (R version 4.3.2, swCRTdesign version 4.0 [22]). The power would be 80.0% if the actual mean difference in the decrease in eGFR is 2.23 ml/min/1.73 m^2^ instead of the originally assumed 2.0 ml/min/1.73 m^2^.

### Recruitment {15}

Hospital data from the past years (2020, 2021) was used to examine the potential of each of the eight medical centres to enrol eligible participants. Achieving the target sample size of *n* = 425 participants based on this data seemed realistic. Moreover, the study schedule included an optional time slot to extend the recruitment beyond 15 months, if necessary.

In November 2022, the first recruitment phase (of control patients) was prolonged by 5 weeks to compensate for a slow start. Because of ongoing underrecruitment especially regarding the intervention group, in October 2023, it was decided to extend the recruitment by four additional phases, 50 days each.

## Assignment of interventions: allocation

### Sequence generation {16a}

According to the cluster-randomised stepped-wedge design, the eight participating medical centres were randomised to eight intervention start times. Randomisation was carried out under the constraint of roughly balanced expected intervention and control group sizes, considering the anticipated recruitment potentials of each medical centres. The allocation sequence was generated by a computer, using a self-written R program and the date as random seed (‘20,220,727’).

### Concealment mechanism {16b}

The randomisation list was concealed from the participating study sites. After randomisation, each medical centre was informed about when it would enter the intervention phase. All switch dates are known to the study group. Subsequent allocation of study participants to the control and intervention groups according to the switch dates is not concealed.

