### Implementation {16c}

Randomisation of clusters was performed at the Institute of Medical Biometry and Statistics, Faculty of Medicine and Medical Center – University of Freiburg, Germany. Participants are enrolled by study nurses. Allocation to the intervention or control group is determined by the stepped-wedge design: At the beginning of the study, all sites recruited into the control group. After the first period, one site switched to intervention conditions. At intervals of 50 days, clusters 2 to 8 also switch to the intervention phase.

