## Statistical methods

### Statistical methods for primary and secondary outcomes {20a}

In the confirmatory primary analysis, the effect of the intervention on the primary endpoint (decrease in eGFR at 12 months) is tested in a linear mixed model, estimated and reported with a one-sided 95% confidence interval ([23]). The model includes the intervention (with versus without modified discharge management), the categorical periods as fixed effects, the baseline measure of eGFR, age at study inclusion and gender as covariates. Intra-cluster variation, i.e. membership of a cluster, is modelled via random intercept. The one-sided test to prove the benefit of the intervention is performed based on the respective one-sided 95% confidence interval from the linear mixed model. Since the follow-up examination will not always take place exactly 12 months after discharge, the decrease in eGFR from the baseline to the follow-up measurement (i.e. the dependent variable in the regression model) is proportionally converted to a 12-month difference.

Intervention effects for binary secondary outcomes will be estimated and tested similarly, using appropriate generalised linear mixed models.

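### Open, judgement-based recruitment can shift case mix at a centre's switch, and the primary model omits diabetes, hypertension and the Charlson Index although all three are collected at baseline

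*Protocol article*

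**What the plan says.** **Allocation.** Centres are randomised to switch times. Within a centre the arm follows from the date, and Concealment mechanism {16b} is open about what that means: "All switch dates are known to the study group", and "Subsequent allocation of study participants to the control and intervention groups according to the switch dates is not concealed". There is no blinding (Who will be blinded {17a}).

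**Entry.** Implementation {16c} says "Participants are enrolled by study nurses". Several steps need judgement:
- The inclusion criteria ask for a general state of health good enough for participation and give no threshold.
- On chronicity, Evaluation of eligibility says: "If chronic renal disease appears certain, the patient will be informed about the study and asked for consent".
- Doubtful cases go to a study physician, including those with critical health conditions, described as "infirm prognosis, the patient may not survive the study" (Consultation (study physicians)).

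**Primary model.** Statistical methods {20a} specifies a linear mixed model with intervention, categorical period, a random intercept for cluster, and "the baseline measure of eGFR, age at study inclusion and gender as covariates".

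**Baseline data.** Under known diagnoses from the hospital information system, Table 1 lists hypertension, diabetes and the "Charlson Index", among others. Background and rationale {6a} names hypertension and diabetes as risk factors for CKD progression. None of the three is in the primary model.

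**The concern.** In a stepped-wedge trial with individual consent, randomising centres does not protect against selection of patients. A nurse decides whom to regard as fit and clearly chronic while knowing whether an appointment will be offered, and patients may respond differently when it is. If the patients enrolled after a centre's switch differ in prognosis from those enrolled before, the difference falls into the treatment contrast.

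The structural terms do not help here. Period effects remove what changes over calendar time in all centres together. The random intercept deals with stable differences between centres. A change in case mix at a centre's own switch coincides with the treatment indicator, so only patient-level covariates can take up any of it. The model has three, and the protocol holds three more that bear on the same judgements about health and prognosis.

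At stake is a one-sided confirmatory test at 5% with a stated power of 72.1%.

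**Working it through.** **1. Inputs from the Sample size {14} section.** Target difference 2 and SD 4 ml/min/1.73 m², ICC 0.02. Second update: 286 patients with complete follow-up, one-sided 5%, power 72.1%, and 80.0% power at a difference of 2.23.

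**2. Do the plan's own figures reproduce?** With fixed periods, a random cluster intercept and a Wald z-test:
- 4 clusters × 5 periods × 17 patients = 340 gives 80.4% power (SD read as residual) or 81.2% (SD read as total), against 80% stated.
- 8 clusters with the stated site sizes give a mean of 87.5% over random orders, as stated.
- The 72.1% cannot be rebuilt, because recruitment by site and period is not given. It does agree with the protocol's other figure. The implied SE is 2 / (1.645 + 0.586) = 0.897, and 0.897 × (1.645 + 0.842) = 2.23.

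The SE of 0.897 is used below.

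**3. Assumed bias.** The documents give no correlation and no comparison of arms, so these inputs are assumptions. Let a prognostic index correlate 0.3 with the eGFR change and differ by 0.2 to 0.4 SD between arms. Both values are meant as what remains after eGFR, age, gender, period and centre.
- Bias = 0.3 × 0.2 × 4 = 0.24, or 0.3 × 0.4 × 4 = 0.48 ml/min/1.73 m². That is 12% to 24% of the target of 2.
- Equivalently, a condition that shifts the 12-month change by 2 and is 12 or 24 percentage points more frequent in one arm: 0.12 × 2 = 0.24 and 0.24 × 2 = 0.48.

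**4. Effect on the one-sided 5% test.** Error = 1 − Φ(1.645 − b/0.897), with b positive when the bias favours the intervention. Power at a true difference of 2 = Φ((2 + b)/0.897 − 1.645).

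| b | b/SE | Error | Power |
|---|---|---|---|
| +0.48 | 0.535 | 13.4% | – |
| +0.24 | 0.268 | 8.4% | – |
| 0 | 0 | 5.0% | 72.1% |
| −0.24 | −0.268 | 2.8% | 62.5% |
| −0.48 | −0.535 | 1.5% | 52.0% |

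Power is left out for positive b because a gain produced by bias is no gain.

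**5. Precision.** If the added covariates explain a further share R² of the variance, the SE shrinks by √(1 − R²), and power = Φ(2.231/√(1 − R²) − 1.645).
- R² = 0.04: Φ(2.277 − 1.645) = 73.6%.
- R² = 0.09: Φ(2.338 − 1.645) = 75.6%.
- Reaching 80% needs R² = 1 − (2.231/2.487)², about 0.195.

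R² is also an assumption; the documents give none.

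**The case against.** The strongest reply is that this is an openly disclosed limitation of the design, that the plan has a pre-specified covariate set, and that preferring a longer one is a matter of taste. Screening starts from diagnosis codes, eGFR and a computed KFRE score, and doubtful cases go to a physician, so the room for judgement is narrower than it may sound. The bias inputs are assumed, the sign is unknown, and the power gain is only 1.5 to 3.5 points.

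Much of this stands, and it limits the point. Four stronger readings may tempt a reader, and the documents do not support them:
- **The omitted variables predict better than those in the model.** No section says so. Diabetes and hypertension are named as risk factors for progression, and that is all.
- **KFRE should be added, also to deal with the change of cut-off.** KFRE is built from age, sex and eGFR, plus the albumin/creatinine ratio in its usual form (Background and rationale), so it largely repeats the present covariates. The cut-off changed on one calendar date, which period effects largely cover, and a subgroup analysis at 15% or above is planned.
- **Selection has been shown, or adjustment would remove it.** Under-recruitment in the intervention group is reported, but it concerns numbers, not case mix, and the control phase had been extended by five weeks. Covariates deal only with measured differences.
- **Balance tables and screening counts are missing.** Exclusions are documented with reasons and a CONSORT flowchart is planned. Further tables are reporting detail that an article may leave out.

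The reply does not remove the core. The article itself fixes the covariate set of the confirmatory model, so this is not a detail left to an analysis plan that is not shown. The set omits collected variables that the protocol's own rationale partly singles out.

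**Conclusion.** The point holds as a risk that is reduced less than it could be, not as a demonstrated bias. The documents establish three things: recruiters know the arm, entry is partly a matter of judgement, and the primary model has no term that could absorb a case-mix change at the switch beyond eGFR, age and gender. The size is conditional. With an assumed remaining bias of 0.24 to 0.48 ml/min/1.73 m² and the SE of 0.897 implied by the protocol, the error moves to about 8% to 13% in one direction. In the other it falls to about 1.5% to 3%, with power down to 62.5% or 52.0%. Which direction applies cannot be told from the protocol, and the share that the three covariates would remove is unknown. The precision gain is a modest secondary benefit.

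**What to change.** Before analysis, and before 12-month results are seen by arm, amend Statistical methods {20a} so that the primary model also contains baseline diabetes (yes/no), baseline hypertension (yes/no) and the Charlson Index as fixed covariates, next to eGFR, age and gender. Leave KFRE out. Date the change: the trial is open, and a covariate set altered after results are visible would raise its own doubts. Overlap among the three does no harm, since their coefficients are not of interest. State in the report that the adjustment covers measured differences only.

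Cost: wording, three further degrees of freedom, and a simple rule for any missing baseline values. No new data are needed, because all three come from the hospital information system. The unmeasured part, such as consent behaviour and unrecorded judgement, remains a limitation.
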